## Abstract

**Background:**

Many physiological health benefits observed after following a ketogenic diet (KD) can be attributed to the associated weight loss. The KD has become more prominent as a popular health choice, not only in obese/overweight individuals, but also in healthy adults. The study aims to determine the effects of a KD, independent of weight loss, on various aspects of physiological health including: sleep, thyroid function, cognition, and cardio-metabolic health. The study will also aim to determine whether a change in basal metabolic rate may be associated with any changes observed.

**Methods:**

Twenty healthy men and women between 18 and 50 years of age will take part in this study. In a randomized controlled, cross-over design, participants will follow two isocaloric diets: a high-carbohydrate, low-fat diet (55% CHO, 20% fat, 25% protein) and a KD (15% CHO, 60% fat, 25% protein). Each dietary intervention will last for a minimum of 3 weeks, with a 1-week washout period in between. Before and after each diet, participants will be assessed for sleep quality, cognitive function, thyroid function, and basal metabolic rate. A blood sample will also be taken for the measurement of cardio-metabolic and immune markers.

**Discussion:**

The present study will help in understanding the potential effects of a KD on aspects of physiological health in healthy adults, without the confounding factor of weight loss. The study aims to fill a significant void in the academic literature with regards to the benefits and/or risks of a KD in a healthy population, but will also explore whether diet-related metabolic changes may be responsible for the changes observed in physiological health.

**Trial registration:**

Pan African Clinical Trial Registry (www.pactr.org), trial number: PACTR201707002406306. Registered on 20 July 2017.

**Electronic supplementary material:**

The online version of this article (10.1186/s13063-018-2462-5) contains supplementary material, which is available to authorized users.

## Background

Obesity, both independently, and in association with other obesity-related diseases, leads to adverse physiological effects of many aspects of health including sleep [1, 2], cognitive function [3, 4], and cardiovascular health [5]. A reduction in body fat is a significant treatment target used to improve obesity-induced adverse effects on each of these physiological health variables [6–8]. However, studies investigating the effect of diet on the physiological aspects of health independent of the loss of weight (whether total mass or fat mass) are lacking. Diets low in carbohydrate and high in fat, or ketogenic diets (KD), are conventionally used to treat epilepsy and neurodegenerative disorders [9, 10], but have been relatively popular for weight loss since the 1800s [11]. Studies on KDs vary in their daily limit of carbohydrate intake; carbohydrate consumption may be restricted to as low as 4% [12, 13] up to 40% [14, 15] of daily caloric intake. The fundamental principle of the KD, however, is severe restriction of dietary carbohydrate consumption, with a concurrent increase in dietary fat to compensate for the energy deficit, resulting in the promotion of lipid oxidation to produce ketones as an energy source (as opposed to glucose), and thus, a metabolic state of nutritional ketosis [16].

Obesity affects various aspects of physiological health, including sleep and cognition. Compared to controls, obese individuals have more night-time wakefulness and less total sleep time [17]. Furthermore obesity with [18] and without [17] sleep apnea is associated with fatigue, daytime sleepiness, and poor sleep quality. A reduction in body fat improves obesity-related adverse effects on sleep architecture and daytime sleepiness [7]. In populations with sleep abnormalities, a KD has been shown to reduce sleepiness [19, 20] and normalize sleep architecture [19, 21] but this change was in association with a loss of body mass, particularly body fat [19]. In healthy, non-obese men who were good sleepers, a KD diet increases slow-wave sleep and decreases rapid-eye-movement sleep [22] compared to a high-carbohydrate, low-fat (HCLF) diet [1]. Studies investigating the effect of the KD on sleep, however, are limited by their study populations and small sample sizes.

Obesity is also a risk factor for dementia and adverse changes to brain structure and function [3]. The relationship between obesity and cognitive decline is likely to be bidirectional, with suggestions that a gain in body fat may, at least in part, be the result of a neurological predisposition characterized by reduced executive brain function, but that obesity further compounds the adverse effects on the brain, possibly via mechanisms involving inflammatory pathways, elevated lipids and/or insulin resistance [8]. There is some evidence to suggest that loss of body mass has the potential to reverse some of the negative obesity-related effects on cognition, particularly with regards to working memory following significant weight loss [12]. Independent of obesity, prospective human studies have identified high-fat diets, particularly diets rich in saturated fats, as risk factors for developing Alzheimer’s disease and dementia [23–26]. Most human studies highlight that specific types of fats are more important than total fat intake; in particular, omega-6 and saturated fatty acids are associated with reduced cognitive performance [24, 27–29]. Randomized controlled trials (RCTs) investigating the effects of the KD on cognition in younger, healthy individuals, are lacking in the academic literature. Therefore, it is yet to be determined whether increased adiposity, or the consumption of high-fat diets, is responsible for cognitive decline.

Dietary effects on cardiovascular function have been investigated more than any other physiological function. However, the majority of studies have been conducted in obese and/or overweight individuals, who are likely to be in an obesity-induced, low-grade pro-inflammatory state. Apprehensions exist that the KD, with its concomitant high intake of total and saturated fat, adversely affects blood lipid levels and hence, increases the risk for cardiovascular disease (CVD) [30–36]. Traditionally, a low-fat diet is prescribed for body fat reduction for obese patients with or at risk for CVD and it is suggested that the fat loss following any diet restriction and/or exercise accounts for the favorable improvements seen in cardiovascular health [37, 38]. However, a meta-analysis on 23 controlled trials involving 1141 obese patients, reported that the KD diet in fact has favorable effects on cardiovascular health [39]. In particular, the KD is associated with significant reductions in plasma triglycerides, fasting plasma glucose, glycated hemoglobin, plasma insulin, C-reactive protein, systolic and diastolic blood pressures, total body mass, abdominal circumference, as well as significant increases in high-density lipoprotein (HDL) cholesterol, with no significant changes in low-density lipoprotein (LDL) cholesterol [39].

The inconsistencies in the results of studies comparing physiological variables between the KD with the current recommended HCLF diet, are further confounded by the fact that total body mass loss is associated with both these diets, particularly with calorie restriction. Given that physiological factors, such as sleep and cardiovascular health, are altered by a reduction in body fat, especially in overweight and obese populations, it is difficult to differentiate between the effects of the loss of fat mass or dietary composition. It is, therefore, important to explore the physiological outcomes of these diets in the absence of any change in body mass.

Further, it is important to note that even with an increase in calorie intake on a KD, a greater loss of body mass has been reported in overweight adolescents compared with those on the HCLF diet, and it has been suggested that a non-calorie restricted KD may be more effective than a very-low-calorie diet due a greater maintenance of metabolic rate, which is a consequence of a higher caloric intake [40]. Despite the most common application for the KD being a reduction in total body mass, there is astonishingly little research investigating the effects of a KD, compared with the conventional HCLF diet, on basal metabolic rate (BMR) or thyroid function [41, 42]. Changes in the thyroid hormones triiodothyronine (T3) and thyroxine (T4) that contribute to maintenance of metabolic rate due to a low-carbohydrate diet have produced mixed results [41–43]. Importantly, however, caloric intake in these studies was not controlled. Instead, greater loss of body mass on the KD compared with HCLF diets, in obese and/or overweight individuals, has been attributed to spontaneous reduction in caloric intake [41, 44, 45], reduced hunger and/or increased satiety due to increased fat consumption [46–49], or an inhibitory effect of β-hydroxybutyrate (BOHB) (the major circulating ketone body) on appetite [50]. Given the persistent metabolic adaptation that follows loss of total body mass and/or calorie restriction, namely adaptive thermogenesis, which promotes an overall decline in energy expenditure and a reduced BMR [51, 52], it is intriguing to determine whether diet composition, independent of a loss of body mass, caloric intake, and levels of physical activity, has any significant metabolic effects.

A controlled, cross-over dietary intervention in healthy individuals, incorporating vital aspects of physiological health into one study and negating the effect of body mass loss and calorie intake, has not yet been done. Given that the majority of studies investigating the KD have: (1) been done in overweight/obese populations, with or without diabetes mellitus and/or insulin resistance, (2) did not control for total caloric intake and levels of physical activity, and (3) did not incorporate a cross-over of subjects doing both diets, this study will account for the many study limitations that exist in the current academic literature by controlling for body mass, existing disease, and calorie intake. Therefore, we wish to determine, in a randomized-controlled cross-over study design, whether a KD, compared with a HCLF diet, affects sleep, cognition, thyroid function, and cardiovascular effects in a generally healthy, non-obese/overweight population while maintaining body mass on the two diets. In addition, we aim to determine whether BMR is different between the ketogenic and HCLF diets in normal healthy adults and whether this difference is associated with any difference in sleep, cognitive and cardiovascular physiology.

## Methods

### Study design

The design of the study is a randomized controlled, cross-over trial. The study will follow the Standard Protocol Items: Recommendations for Interventional Trials (SPIRIT) guidelines for the design and conduct of a trial (Fig. 1; Additional file 1) [53]. As outlined in Fig. 2, participants will be asked to visit the Movement Physiology Research Laboratory on five occasions; the first visit will be for screening the volunteers to ensure that they fit the study criteria. Thereafter, eligible participants will return to the laboratory before the start of, and after, each dietary intervention. Following 1 week of normal habitual dietary monitoring, each participant will follow two isocaloric diets (a KD and a high-carbohydrate, low-fat (HCLF) diet) in a randomized order and separated by a 1-week washout period. Randomization of the order of the diets will be done using the Microsoft Excel 2010 (Version 14.0) CHOOSE and RANDBETWEEN functions. These functions (=CHOOSE(RANDBETWEEN(1,2), “A”,“B”) are able to assign each new participant into one of the two diets. Each dietary intervention will last for a minimum period of 3 weeks. In the KD it is critical for the participant to remain in a ketogenic state for three consecutive weeks. Should the participant leave the ketogenic state (as assessed by blood ketone levels), the dietary intervention period will be prolonged until the consecutive, 3-week ketogenic state is achieved. If a participant does not reach a ketogenic state in 2 weeks, we will exclude them, as it is indicative of non-compliance. However, we will be more lenient with someone who has entered a ketogenic state but may struggle to maintain the state, in which case we will guide them by closely monitoring their diet to ensure that their carbohydrate intake is suitably low and that their fat intake is suitably high. We will also look at the content of each participant’s diet to ensure that the foods do not contain imperceptible carbohydrates or that their protein content is not too high, which may result in gluconeogenesis. We will continuously encourage pure fat intake, e.g., cooking with olive oil, butter or coconut oil. Should a participant leave the ketogenic state more than five times they will be excluded from the study.

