**Fig. 2 Fig2:**
[figure not shown]
Timeline and details of study procedures

The principal investigator (PI) who is collecting the outcome measures will not be blinded to the diet allocation because feedback may need to be provided on a daily basis, to encourage dietary compliance. A researcher that will conduct the statistical analysis will, however, be blinded to the order in which the diets were undertaken.

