### Participants

Twenty healthy individuals, between the ages of 18 and 50 years, will be asked to volunteer in this study. A total of 20 participants would provide 85% power to obtain a medium effect size for BMR (Cohen’s *d* effect size = 0.3) [54]. Using standardized and customized screening questionnaires for sleep quality and general health, volunteers will be screened to ensure that they are free from any chronic illness, depression, sleep disorders, for at least 6 months prior to the start of the study. Volunteers will be excluded if they are overweight or obese (BMI ≥ 26 kg/m^2^), have any adverse cardiac or metabolic conditions such as type 1 or 2 diabetes mellitus, hypercholesterolemia or hypertension confirmed by a clinician. The Pittsburgh Sleep Quality Index (PSQI) [55] and the General Health Questionnaire (GHQ) [56] will be used to assess quality of sleep and psychological health, respectively. Eligible participants will be asked to maintain the same level of physical activity throughout the study, which will be monitored using the standardized Global Physical Activity Questionnaire (GPAQ) [57]. If participants are taking a daily vitamin/mineral supplement, they will be asked to continue taking it as usual. If they are not taking any supplement they will be asked not to start taking one during the study. Using the dietary data obtained from 1 week of habitual dietary monitoring at the start of the study, daily calorie intake will be calculated for each participant and the total amount of calories consumed daily during both dietary interventions will be based on this value.

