### Data analysis

Data analysis will be done using IBM SPSS Statistics (version 24, IBM Corporation, NY, USA). A two-tailed statistical significance will be accepted at *P* < 0.05. Each outcome variable assessed will be analyzed according to diet (KD or HCLF) and time (before and after each diet) using a repeated-measures two-way analysis of variance (ANOVA). Where appropriate, a Student-Newman-Keuls post-hoc test will be used to assess the origin of any significant differences detected by the ANOVA models. Variables will be adjusted for potential confounders which will be determined using multiple linear regressions. A power analysis has indicated that total of 20 participants would provide 85% power to obtain a medium effect size for BMR (Cohen’s *d* effect size = 0.3) [54].

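### Diet order comes from an unrestricted 1:1 draw in a 20-person cross-over, and the stated analysis has no period or sequence term to absorb the likely imbalance

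*Protocol article*

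**What the plan says.** All references are to the protocol article.

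- **Size (Participants):** "Twenty healthy individuals, between the ages of 18 and 50 years, will be asked to volunteer in this study".
- **Design (Study design):** each person follows both diets "in a randomized order and separated by a 1-week washout period".
- **Allocation (Study design):** "Randomization of the order of the diets will be done using the Microsoft Excel 2010 (Version 14.0) CHOOSE and RANDBETWEEN functions". The printed formula begins "CHOOSE(RANDBETWEEN(1,2", returns A or B, and the functions "are able to assign each new participant into one of the two diets". No block, stratum, target split or seed is given.
- **Blinding (Study design, text below Fig. 2):** the principal investigator "will not be blinded to the diet allocation because feedback may need to be provided on a daily basis". The researcher who runs the analysis is kept unaware of diet order.
- **Model (Data analysis):** each outcome "will be analyzed according to diet (KD or HCLF) and time (before and after each diet) using a repeated-measures two-way analysis of variance". Neither period nor sequence is named. Confounders are to be identified by regression, without a list.
- **Measurement (Laboratory assessments, Outcomes):** outcomes are taken before and after each diet, and the primary outcome is the change that a diet induces.

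**The concern.** A two-period cross-over compares the diets within person, but each diet is taken in a different period. Anything that differs between the first and second period is removed from the diet comparison in one of two ways: equal numbers in each order, or a period term in the model. The stated plan secures neither. The draw leaves the split to chance, the model has only diet and time, and the analyst is not to know the order, which is the variable that a period adjustment needs.

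The Cognitive function section itself recognizes a learning effect, and cognition is part of the primary outcome. If improvement slows with repetition, the gain from before to after is larger in the first period than in the second. With unequal orders, part of that difference would be read as an effect of diet.

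**Working it through.** **Plan's own figure.** The article states none for sequence balance. Its 85% power for BMR does not enter the argument; 85% serves below only as a nominal starting point.

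**Inputs.** n = 20 (Participants); probability 0.5 per draw, draws independent (printed formula, Study design); factors diet and time only (Data analysis). A or B is taken to mean the diet given first. The size of a period effect is an assumption, shown as a range.

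**Step 1: chance of imbalance.** The number k taking one given order is Binomial(20, 0.5).
- P(10:10) = C(20,10)/2^20 = 184756/1048576 = 17.6%.
- P(unequal) = 100% - 17.6% = 82.4%.

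**Step 2: what is left in the contrast.** Let t be the true KD minus HCLF difference in within-period change. Let p be the amount by which within-period change in period 2 exceeds that in period 1, whatever the diet. A KD-first participant has expected difference t - p, and an HCLF-first participant t + p. With k people KD-first, the average over 20 is

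t + p(20 - 2k)/20,

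so the share of p left in the diet-by-time contrast is |2k - 20|/20. A level shift that raises the before and after values of a period equally drops out of the change, so it contributes nothing to p.

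**Step 3: precision once period is adjusted for.** The variance relative to 10:10 is (1/k + 1/(20-k))/(2/10). At 14:6 this is (0.0714 + 0.1667)/0.2 = 1.19.

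| Split | P(this split or worse) | Share of p left | Artefact if p = 0.2 SD | Artefact if p = 0.5 SD | Variance ratio |
|---|---|---|---|---|---|
| 11:9 | 82.4% | 0.10 | 0.02 SD | 0.05 SD | 1.01 |
| 12:8 | 50.3% | 0.20 | 0.04 SD | 0.10 SD | 1.04 |
| 13:7 | 26.3% | 0.30 | 0.06 SD | 0.15 SD | 1.10 |
| 14:6 | 11.5% | 0.40 | 0.08 SD | 0.20 SD | 1.19 |
| 15:5 | 4.1% | 0.50 | 0.10 SD | 0.25 SD | 1.33 |

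SD here is the SD of within-period change. Averaged over the binomial distribution (both orders present), the variance ratio is 1.06. If a period-adjusted analysis had about 85% power at 10:10, it would have 83.4% at 12:8, 81.4% at 13:7 and 78.2% at 14:6.

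**The case against.** Several objections carry weight.

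- **Simple randomization is valid.** This stands. The sign of the imbalance is itself random, so the comparison is unbiased on average. The artefact is conditional on the split obtained.
- **Most splits are mild.** This stands. A split of 11:9 or better has probability 100% - 50.3% = 49.7%, and 12:8 or better 100% - 26.3% = 73.7%. Precision loss alone would not justify the point.
- **Before-and-after measurement already protects.** This stands in part. A pure level shift cancels. A difference in change between periods does not, and learning that slows with repetition is of that kind. The practice runs planned for the habitual week should reduce it, but the article gives nothing to show that it disappears.
- **The confounder clause, or an analysis plan not shown, might bring period in.** It might. As written, though, the model names only diet and time, and the analyst is not given order. If period is added, only the small loss of precision remains.

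A reader might go further and infer that allocations were never fixed, that there is no audit trail, or that a draw could be repeated unseen. The documents do not support this. The article does not say how results were stored, concealed or released, or who ran the sheet, and an article commonly leaves such detail to the full protocol. Nor does the unblinded principal investigator show selective allocation: the reason given is daily dietary feedback, which comes after allocation and says nothing about control of the draw.

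**Conclusion.** The point holds as a weakness in the stated combination of allocation and analysis. With 20 participants and independent even draws, unequal orders are likely (82%), and a split of 14:6 or worse has about a one-in-nine chance (11.5%). At 14:6, 40% of any between-period difference in within-period change remains in the diet-by-time contrast: 0.08 to 0.20 SD of change if that difference is 0.2 to 0.5 SD. That range is an assumption, because the documents give no period effect; with no such difference there is no artefact. The variance cost is minor (about 6% on average, 19% at 14:6).

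It would be wrong to infer that the randomization is invalid, or that any period effect would bias the result. The first is untrue on average, and the second fails for level shifts. The reason to act is that both safeguards are cheap and the stated plan has neither.

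**What to change.** **Allocation.** Replace the per-participant draw with one pre-generated restricted list for 20 places: permuted blocks of varying size giving 10:10 overall (for example two blocks of 4 and two of 6, in random order: 8 + 12 = 20). Release it one participant at a time after baseline.

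**If some participants are already allocated.** Keep those allocations. Fill the remaining places from a single random permutation holding the numbers of each order needed to reach 10:10, or as near as possible. For illustration, after 8:4 the last eight places would hold two and six. Balanced blocks from that point would only preserve the existing imbalance. Trial status puts the start of recruitment in May 2017 and the end of data collection in February 2018, so few or no places may remain. In that case the model change below is the whole remedy.

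**Analysis.** Add period in any case, because the exclusions described under Study design can unbalance the completers even from a 10:10 start. In a diet-by-time model this means period and its interaction with time or, equivalently, period as a factor in an analysis of within-period change. Supply order to the analyst under coded diet labels, and amend the blinding statement to match.

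**Cost.** About an hour to prepare the list, one added model term, and no extra visits. The last assignments become somewhat more predictable, which matters little because every participant is to receive both diets.
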